## Introduction

### Overview

Rotator cuff pathology is the most common cause of shoulder pain and disability [1,2], and it is associated with significant utilization of health care resources [3] and societal and economic costs [1]. Exercise-based physiotherapy is the established first-line treatment for this condition [4-6] and is also a critical element of rehabilitation following rotator cuff surgery [7,8]. Adherence to prescribed physiotherapy is essential for successful rehabilitation in both conservatively and operatively managed patients [9,10]. However, adherence to physiotherapy is often poor [9,11], particularly in the home setting [9,12,13] and in worker populations [10]. Currently, there are no established methods to effectively and objectively measure adherence to home shoulder physiotherapy [12,14]. Thus, the rate and quality of participation with home shoulder therapy and the relationship between adherence and recovery are unknown.

We have developed the Smart Physiotherapy Activity Recognition System (SPARS), a novel solution for measuring adherence to home shoulder physiotherapy from inertial sensor data recorded on a smart watch using state-of-the-art machine learning (ML) techniques [15]. SPARS was shown to classify exercises for participation monitoring with high (99.99%) accuracy in 20 healthy adults.

The proposed study will further develop and validate our technology to assess home shoulder physiotherapy adherence to both participation and technique in a population with rotator cuff pathology. We will measure the rate of adherence, establish the relationship between adherence and recovery, and explore possible patient factors predictive of poor home physiotherapy adherence. In addition, we will examine ethical and related policy issues associated with the deployment of this technology, specifically investigating patient privacy, individual rights, clinical decision making, health resource allocation, and policy in the setting of artificial intelligence–based surveillance of patient self-management strategies. Guided by ethical analysis and a user-centered design process, we will develop and pilot test a conscientious rehabilitation program with individualized adherence-driven patient care.

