#### Aim 2: Measure the Rate of Adherence to Home Shoulder Physiotherapy, the Relationship Between Adherence and Recovery, and Identify Barriers to Home Physiotherapy Adherence

##### Objectives

The related objectives are as follows:

Inertial sensor data are collected during home physiotherapy for 120 patients with rotator cuff pathology over full treatment duration (up to 5 months).Technical failures preventing home data collection are less than 5%.Clinical outcomes: return to work status, shoulder range of motion, rotator cuff strength, and patient-reported outcomes of pain and disability are collected pretreatment, monthly through treatment (up to 5 months), and at 12-months final follow-up. The final follow-up exceeds 85%.A total of 23 potentially significant predictors of home physiotherapy adherence (identified in Methods: Barriers to Adherence) are collected for all study participants at the time of recruitment.

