### Data Analysis

#### Sample Size

The proposed sample size of 120 for clinical validation yields a power of 80% to detect weak correlations (*R*>0.25) between physiotherapy adherence and clinical outcomes, accepting a 5% alpha error. Sample size feasibility was confirmed by the WCP, anticipating a recruitment rate of 70%. The pilot study sample size (20) was used to detect implementation challenges with an incidence rate greater than 15% at a 95% confidence level [124] (not statistically significant differences in clinical or economic outcomes).

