#### Univariable and Multivariable Analyses

The relationship between adherence (dependent variable) and individual baseline adherence predictor variables and environment (home or clinic) will be examined using parametric univariable statistical analyses, linear regression for continuous predictors, and 2-sample *t* tests and analysis of variance for binary and multiclass categorical predictors. A multivariable analysis will be conducted to model adherence from statistically significant predictors (maximum 12) and evaluate their relative importance.

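### The barriers model is built from predictors that pass univariable significance tests and is refitted in the same 120 patients, with no allowance for selection from 23 candidates

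*Protocol article*

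**What the plan says.** The Aim 2 objectives announce "A total of 23 potentially significant predictors of home physiotherapy adherence", collected at recruitment. The list under Barriers to Adherence in the Methods agrees: 22 items, or 23 if tear thickness and tear size count separately.

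Under Univariable and Multivariable Analyses, the relationship of adherence to each predictor, and to environment (home or clinic), "will be examined using parametric univariable statistical analyses, linear regression for continuous predictors", with t tests and analysis of variance for categorical predictors. The next step is: "A multivariable analysis will be conducted to model adherence from statistically significant predictors (maximum 12) and evaluate their relative importance". The only tests that come before this model are the univariable ones, so significance there is the entry rule.

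The section states no threshold. For this model the article mentions no multiplicity control, forced-in terms, shrinkage or internal validation. The cross-validation under Construct Validity concerns the exercise classifiers.

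The Overview describes the purpose of this part as to "explore possible patient factors predictive of poor home physiotherapy adherence".

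**The concern.** The same patients choose the predictors, supply their coefficients and rank them. A predictor enters only if its observed association happens to be large enough, and the final P values, intervals and importance ranking are then read as if the model had been chosen without looking at the data. Noise predictors that pass the screen arrive with a large observed effect, and weak true predictors tend to be kept in the samples that overstate them.

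The cap of 12 does not cure this. It gives 120/12 = 10 patients per retained term, but the search runs over 23 candidates, 120/23 = 5.2 patients each. It also counts predictors rather than parameters, although the section itself expects multi-category predictors.

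At stake is the reliability of the list of barriers, which is part of the Aim 2 title. This is not a detail deferred to an analysis plan, because the article fixes the selection rule.

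**Working it through.** **Inputs.** N = 120, power 80%, R > 0.25 and alpha 5% (Sample Size); 23 candidates (Aim 2 objectives); entry on univariable significance with at most 12 kept (Univariable and Multivariable Analyses). Assumed: a two-sided 0.05 threshold for the screen and, in simulation, continuous candidates with the effect sizes and correlations stated below.

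**The plan's own figure.** The article says that N = 120 "yields a power of 80% to detect weak correlations". Power = Φ(atanh(r)·√(N−3) − 1.96). With r = 0.25: 0.2554 × 10.817 − 1.96 = 0.803, so power is 78.9%. This agrees with the stated 80%; the smallest r with 80% power at N = 120 is 0.253. The calculation concerns "weak correlations (*R*>0.25) between physiotherapy adherence and clinical outcomes", not the barriers model.

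**False selections if no predictor matters (independent tests).**
- Expected number: 23 × 0.05 = 1.15.
- At least one: 1 − 0.95^23 = 69%. At least two: 32%.
- With 22 candidates: 1.10 and 68%. With 24 (adding environment): 1.20 and 71%.
- If participation and technique adherence are both screened, 46 tests: 46 × 0.05 = 2.3 and 1 − 0.95^46 = 91%.

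**What passes the screen.** The smallest significant correlation is tanh(1.96/√117) = 0.18. A true predictor passes with probability 37% (r = 0.15), 59% (r = 0.20) or 79% (r = 0.25).

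**Simulation, independent candidates, 4 of 23 true at 0.20.** The comparator is a 12-term model fixed in advance that contains all four true predictors.

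| | Screening | Fixed model |
|---|---|---|
| Mean estimate / true value, true predictors in the model | about 1.20 | 1.00 |
| 95% interval coverage | about 38% (retained noise predictors) | 95% |
| At least one false predictor | 63% | 32% |
| True predictors missed | 41% | 39% |
| R-squared, apparent / new data | 0.19 / 0.04 | 0.24 / 0.06 |

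False means retained by the screen or, in the fixed model, P < .05; missed means the reverse.

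**Independent candidates, 5 true.** Screening gives ratios of 1.49, 1.19 and 1.05 for true coefficients of 0.15, 0.20 and 0.25, with coverage over all retained terms of 74%, 84% and 89%. A model holding all 23 gives 1.00 and about 95% throughout. At 0.20, the sets selected in two replicate studies overlap by 32% on average (Jaccard index).

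**Candidates correlated at 0.2.** With 5 true at 0.15 to 0.20, the ratio is 0.89 to 0.92 and coverage over all retained terms is 96% to 97%, so there is no inflation and no shortfall in coverage. However, 5.6 to 6.9 non-causal predictors are kept per trial, and apparent R-squared is 0.27 to 0.42 against 0.12 to 0.29 in truth. In the corresponding check with 4 true predictors the figures are 0.31 and 0.18.

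**The case against.** The strongest reply is that several of these faults are not caused by screening, and much of it stands.

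- **Missed barriers.** A reader might infer that screening discards about 40% of true barriers. A fixed model fails to find nearly as many (39% against 41%). The cause is low power for r = 0.20 at N = 120.
- **Optimistic R-squared.** A fixed 12-term model is optimistic too (0.24 against 0.06), and its small advantage in new data requires that it contain all four true predictors. With two of the four, new-data R-squared falls to about −0.03, below screening.
- **Inflation.** A reader might infer that importance is always overstated. It is not when candidates correlate at 0.2, and correlation is plausible among education, income, job demands, self-efficacy and social support. Moreover, looking only at significant coefficients inflates the fixed model as well (28%).
- **False inclusions.** Part of the 63% against 32% contrast arises because the fixed model tests 8 null predictors rather than 19.
- **Use of the results.** A reader might infer that the model is meant to steer resource allocation or the Aim 3 program. The ethics section says only that patient profiles could be used for allocation, and the program design section relies on qualitative ethical and policy analysis and knowledge translation. The Aim 2 hypotheses include none on barriers.
- **Prior evidence.** Factors Affecting Adherence is a thin basis for a fixed model. Most of its evidence concerns clinic appointments, and only some of its factors are among those collected.

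What survives is that coefficients, intervals and ranks are reported with no allowance for selection. Calling the aim exploratory lowers the consequence but does not make those figures valid.

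**Conclusion.** The concern holds in limited form. The rule lets chance help choose the barriers: on average 1.15 null predictors pass if none matters, and at least one passes in 69% of studies. With weak, nearly independent predictors it overstates retained true coefficients by about 20% (5% to 49% over the effect sizes tried), and intervals for retained noise predictors cover about 38% of the time. With candidates correlated at 0.2 the harm is different: non-causal predictors are listed as barriers in their own right and R-squared is optimistic.

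These figures rest on an assumed 0.05 threshold, independent tests for the 1.15 and 69%, and assumed effect sizes with continuous predictors. The documents do not support attributing missed barriers to screening, or claiming general inflation.

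Severity is low to moderate, because the article describes the aim as exploratory and mentions use in resource allocation only as a possibility.

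**What to change.** Stop using univariable P values to decide entry, and adopt one of two routes before adherence is related to the predictors.

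1. Fix a model in advance on subject-matter grounds, fit it once and keep every term. Factors Affecting Adherence supports only some of the terms; others may be chosen from the list under Barriers to Adherence. Apply the limit of 12 to parameters, not predictors. Report coefficients with confidence intervals.
2. Fit a penalised regression to all 23 candidates and report the shrunken coefficients.

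On either route, repeat the whole procedure in bootstrap samples and report an optimism-corrected R-squared, the stability of importance ranks and, where terms are selected, of selection. Univariable results can still be shown descriptively. Label the barriers list exploratory.

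The cost is a change of analysis wording and slightly more analysis work; no new data or patients are needed. Some candidates become secondary on the first route. Little or no predictive gain should be expected, and a poorly chosen fixed model can predict worse than screening. The gain is in honest coefficients, intervals and ranks.

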#### Algorithmic Fairness

Equalized odds and equal opportunity fairness metrics [127] will be calculated for adherence classifiers on selected subgroups (sex and workers’ compensation status). Fairness-aware classifier training with prejudice regularization [128] will be considered if needed to produce fair results.

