### Adherence to Rotator Cuff Rehabilitation

Several studies on patients with rotator cuff pathology have measured rehabilitation adherence variables, including clinic attendance, adherence to postoperative restrictions, and home physiotherapy participation during rotator cuff rehabilitation [4,10,13,26,49-51]. Nonadherence (eg, to protective device use and clinic attendance) is more prevalent in workers’ compensation patients (52%) than nonworkers (4%) [10]. There is also a relationship between adherence and improved clinical outcomes in the nonoperative [50] and operative management [10,51] of rotator cuff pathology.

Unfortunately, adherence to home rotator cuff exercises has only been measured with adherence diaries [4,26,50] or in response to directed questioning [51]. The completion rates for the adherence diaries varied from 60% to 75% [4,26,50]. Furthermore, the validity of a patient’s self-reported adherence is questionable as a research instrument [52]. Therefore, the rate and effect of adherence to home rotator cuff exercise participation and technique remain unknown. The proposed study will address this knowledge gap in a cohort of 120 patients with rotator cuff pathology.

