#### Barriers to Adherence

The following potentially significant adherence predictors [12,105-110] will be collected for each patient at recruitment: age, sex, body mass index, dominant side involvement, symptom duration, mechanism of injury (traumatic or degenerative), rotator cuff tear thickness and size, type of operative procedures, comorbidity (cumulative illness rating scale [111]), smoking status, alcohol intake, opioid intake, cannabinoid intake, the baseline level of physical activity, education, marital status, job demands, socioeconomic status (current income), perceived social support (Enhancing Recovery in Coronary Heart Disease Social Support Inventory [112]), patient self-efficacy (2-item Pain Self-Efficacy Questionnaire [113]), Patient Expectation Questionnaire [114], and Hospital Anxiety and Depression Scale [115].

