#### Criterion Validity

Changes in clinical outcomes will be evaluated as a function of SPARS adherence measures using univariate linear regression analysis, with management subgroup (conservative or operative) and population subgroup (worker or patient) as moderators. This analysis will examine both the concurrent and predictive effects of home physiotherapy adherence on clinical outcomes.

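### The only fairness remedy named does not target the error-rate metrics the plan checks, and if used it can shrink true group differences in measured technique adherence

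*Protocol article*

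**What the plan says.** All references are to the protocol article.

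- **Algorithmic Fairness, the check:** "Equalized odds and equal opportunity fairness metrics [127] will be calculated for adherence classifiers on selected subgroups", the subgroups being sex and workers' compensation status.
- **Algorithmic Fairness, the remedy:** "Fairness-aware classifier training with prejudice regularization [128] will be considered if needed to produce fair results". No other remedy is named, and no penalty strength is set.
- **Home Physiotherapy Technique Adherence:** technique is a binary label, and the output of the trained technique classifier on home data is the measure of technique adherence.
- **Barriers to Adherence:** the baseline predictors begin with "age, sex, body mass index, dominant side involvement, symptom duration". Compensation status is not in the list.
- **Univariable and Multivariable Analyses:** adherence is the dependent variable and is tested against those predictors.
- **Criterion Validity:** the regression of outcome change on adherence takes management subgroup and "population subgroup (worker or patient) as moderators".

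No section reserves an unadjusted classifier for the last two analyses.

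**The concern.** The check and the remedy have different targets. Equalized odds and equal opportunity condition on the true label, so they allow one group truly to perform its exercises less well than another. A penalty on dependence between prediction and group does not condition on the truth. It pulls the predicted rates together whether their difference comes from classifier error or from real behaviour.

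In many uses of a classifier that is a policy choice. Here the classifier is the measuring instrument. If the penalty is applied, a true difference in technique between men and women can be shrunk in training, before adherence is regressed on sex. The error-rate gap that prompted the remedy may also widen.

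**Working it through.** The plan states no figure on this point, so there is none to reproduce. The document does not define prejudice regularization. The check uses its ordinary definition, a penalty on the mutual information between prediction and protected attribute. All rates below are assumed unless a source is given.

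**Step 1. Identity.** With true rate p, true-positive rate TPR and false-positive rate FPR:

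predicted rate = p × TPR + (1 − p) × FPR.

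If TPR and FPR are equal in two groups, the predicted rates differ by (p1 − p0) × (TPR − FPR). That is zero only if p1 = p0 or TPR = FPR. With p = 40% and 20%, TPR 0.9 and FPR 0.1:

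- 0.40 × 0.9 + 0.60 × 0.1 = 42%
- 0.20 × 0.9 + 0.80 × 0.1 = 26%

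The equalized-odds gap is 0, yet predictions differ by 16 points, and the penalty acts on that difference.

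**Step 2. Simulation of the penalty.** There were 40,000 records. The smaller group's share was 9/46, the compensation share in the Recruitment section. True event rates were 40% (smaller group) and 20%. Signal quality was the same in both groups (separation 2.56 SD). The classifier was logistic with separate weights per group and a cut-off of 0.5, and the loss was log-loss + η × mutual information (plus a negligible ridge term). Each pair gives the smaller group first; gaps are in points.

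| η | Mean predicted rate | Difference | TPR | TPR gap | FPR |
|---|---|---|---|---|---|
| 0 | 40.1% vs 20.1% | 20.0 | 0.874 vs 0.771 | 10.3 | 0.077 vs 0.034 |
| 1 | 35.6% vs 21.0% | 14.6 | 0.807 vs 0.792 | 1.5 | 0.049 vs 0.039 |
| 5 | 28.3% vs 22.2% | 6.1 | 0.655 vs 0.810 | 15.5, reversed | 0.016 vs 0.045 |
| 100 | 23.1% vs 22.7% | 0.4 | 0.499 vs 0.819 | 32.0, reversed | 0.005 vs 0.049 |

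A light penalty improves the plan's metric but costs about a quarter of the true difference. Stronger penalties remove most of the difference and make the TPR gap worse than at the start.

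**Step 3. Would group-specific thresholds do instead?** Take true correct technique of 80% (non-workers) and 60% (workers), with TPR/FPR of 90%/20% and 85%/20%.

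- Measured, non-workers: 0.80 × 0.90 + 0.20 × 0.20 = 76%.
- Measured, workers: 0.60 × 0.85 + 0.40 × 0.20 = 59%. The difference is 17 points against a true 20.
- Under an equal-variance binormal model, the workers' d' is z(0.85) + z(0.80) = 1.04 + 0.84 = 1.88. Moving their threshold to a TPR of 90% gives FPR = Φ(1.28 − 1.88) = 27.5%.
- Their measured rate becomes 0.60 × 0.90 + 0.40 × 0.275 = 65%. The difference falls to 11 points and an FPR gap of 7.5 points opens.

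Thresholds alone therefore need not equalise both error rates, and they can also shrink the difference.

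**Step 4. Correcting the measured rate.** Solving the identity for p gives p = (measured − FPR) / (TPR − FPR). For the same example:

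- Non-workers: (0.76 − 0.20) / (0.90 − 0.20) = 80%.
- Workers: (0.59 − 0.20) / (0.85 − 0.20) = 60%.

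The true rates are recovered without any penalty, provided the group-specific error rates from labelled sessions carry over to home data.

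**The case against.** The strongest reply is that the plan commits to nothing harmful. The remedy is optional and its strength is open. The only yardstick in the section is "Equalized odds and equal opportunity fairness metrics", so a classifier that worsened those metrics would hardly count as fair. The light-penalty row in Step 2 shows that the remedy can serve the stated metric. This stands, and it limits the point to what can happen if the remedy is used. It does not remove it, because even the light penalty attenuated the group difference and nothing in the document keeps unpenalised output for the adherence analyses.

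Four stronger readings are tempting, and the documents do not support them:

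- **That group differences will be erased.** This needs a near-complete penalty, which no section proposes.
- **That the protocol expects a large true gap in technique by compensation status.** The 52% against 4% in Adherence to Rotator Cuff Rehabilitation is nonadherence to matters such as device use and clinic attendance. The same section says that adherence to home exercise and technique is unknown.
- **That power for a worker versus non-worker comparison of mean adherence would collapse.** Compensation status is not a listed predictor, so the plan names no such test.
- **That the moderator result would be an artefact.** Worker status moderates the slope of outcome on adherence, and a shift in a group's mean adherence does not by itself change that slope. Altered group-specific error rates could rescale measured adherence by TPR − FPR and so affect the slope, but no size for this has been shown.

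Participation adherence is also touched only indirectly, since it counts recognised exercises against those prescribed.

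**Conclusion.** The point holds as a mismatch between check and remedy. The plan judges fairness by error rates given the truth but names only a remedy that, as ordinarily defined, penalises dependence on group. If that remedy is used and true rates differ by group, it can attenuate the measured difference. At a strong penalty it can worsen the metric it was meant to repair.

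The concern is direct for the binary technique classifier and for the comparison by sex. It is less clear for worker status as a moderator, and indirect for participation.

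No size for this trial can be derived from the documents. The simulated range, a 20-point difference falling to between 14.6 and 0.4 points, is illustrative. It rests on the assumed true rates, equal signal quality, separate weights per group and the mutual-information form of the penalty. This is a limited, conditional defect that is cheap to close before any classifier is adjusted.

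**What to change.** 1. In Algorithmic Fairness, replace prejudice regularization with training constrained on true- and false-positive rates. Accept an adjusted classifier only if the equalized-odds metrics improve on labelled sessions.
2. State that the analyses under Criterion Validity and under Univariable and Multivariable Analyses use output that carries no group-dependence penalty.
3. Add a sensitivity analysis that corrects measured technique rates with the group-specific true- and false-positive rates from labelled sessions, as in Step 4.
4. Do not rely on group-specific thresholds alone, for the reason shown in Step 3.

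The cost is a few sentences in the plan and slightly more analysis work. The main downside is imprecision. At the recruitment share reported so far (9 of 46), about 120 × 9/46 ≈ 23 of 120 patients would have a compensation claim, so error rates in that group will be poorly estimated and should be reported with their uncertainty.
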